#### Cognitive bias analyses

Cognitive bias scores will be calculated from reaction time (RT) data from the visual probe task, by subtracting RTs to probes that replace smoking-related pictures from RTs to probes that replace neutral pictures, so that positive scores represent a bias towards smoking cues and negative scores represent a bias towards neutral cues. These bias scores will be used to examine cognitive training effects in a two (pre- and post-CBM) × two (varenicline and placebo) × three (attend, avoid, and control) mixed-model ANOVA.

A two (smoking cue and neutral cue) × two (pre- and post-CBM) × two (varenicline and placebo) × three (attend, avoid, and control) mixed-model ANOVA will also be conducted on the modified Stroop task RT and error data. Participants will be excluded if their mean RT or error score is three standard deviations (or more) below or above the sample mean.

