Recent research indicates that it is possible to reduce cognitive biases using computer-based cognitive bias modification (CBM) paradigms that train individuals to allocate attention away from disorder-relevant cues. CBM has been shown to reduce cognitive biases in anxiety and depression [15–17] and has also been associated with reduction in other symptoms [18]. Attwood *et al*. [19] investigated the effect of a single session of stimulus-avoidant CBM using a modified dot-probe task, and reported decreases in cognitive bias in daily smokers. Compared to a group who had been trained to attend to smoking cues, there was evidence that the avoid group also showed attenuated craving in response to *in vivo* smoking cues in a subsequent cue exposure test (male participants only). The current study will extend earlier work by investigating the neural responses to smoking-related cues following CBM. The neuroimaging literature suggests that drug-related cognitive biases are the results of a failure of cognitive regulatory systems to increase control in the presence of salient cues that increase processing in the reward and emotional centers of the brain (such as the striatum and amygdala) [20]. These data will enable the investigation of whether CBM decreases emotional responses to drug-related cues or increases cognitive control in their presence, and will thereby increase understanding of the mechanisms that underlie CBM effects.

There has been a recent suggestion that the smoking cessation pharmacotherapy varenicline reduces cue-induced craving and cue-induced reinstatement of drug-taking in animals [21–24]. This study will include a pharmacological challenge that randomizes participants to receive seven days treatment of either varenicline or placebo prior to a functional Magnetics Resonance Imaging (fMRI) scan, in order to assess neural cue-reactivity following varenicline treatment. Previous research has reported differences in neural response to smoking cues following varenicline treatment [25], but the sample sizes were small and the effects require replication.

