### Randomization

Participants will be randomly assigned to drug and CBM groups, but equal numbers of participants per group will be maintained. The drugs will be prepared by University Hospitals Bristol Pharmacy who will produce two batches of 36 bottles (one for males and one for females) that comprise 18 bottles of varenicline and 18 bottles of placebo. Each bottle will be given a numeric identifier that enables study staff involved in data collection to be fully blinded to drug condition.

In advance of the study, an experimental collaborator (who will have no direct contact with the study participants) will prepare a numeric code using random number assignment software to further randomize participants to CBM groups. Randomization will be stratified so that equal numbers of male and female participants will be allocated to each experimental cell.

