### Outcome measures

Primary outcome measures are changes in cognitive bias as measured by the visual dot-probe task, and neural responses to smoking-related cues. Secondary outcome measures will be cognitive bias as measured by a transfer task (modified Stroop test) and subjective mood and cigarette craving as measured by the Questionnaire of Smoking Urges (QSU) and the Minnesota Nicotine Withdrawal Scale (MNWS). Measures and materials.

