#### Cognitive bias modification

For the CBM, participants will be randomized to complete a version of the visual probe task designed to induce a biased cognitive response away from (avoid: n = 24), or towards (attend: n = 24) smoking-related cues, or a control condition (control: n = 24) designed not to modify cognitive bias. Each task version comprises a total of 768 trials. On each trial, following a 500 ms duration fixation cross, a picture pair is presented on a computer screen for 500 ms. When this picture pair disappears, a probe is presented in either of the two screen locations previously occupied by a picture. This probe is either a small circle or square. Participants are required to discriminate between the identity of each probe by pressing the arrow keys on the keyboard as appropriate, and the response latency is measured. The majority (n = 512) of trials are training trials, presented in four blocks, and the remainder (n = 256) of trials are test trials. Half of the test trials (n = 128) are presented prior to the training trials, and half (n = 128) after the training trials, in order to assess the effect of the training trials on cognitive bias. In the test trials, the probe appears with equal frequency in the vicinity of both the smoking-related or neutral pictures. In the training trials, the probe appears in the vicinity of the neutral picture on 75% of trials in the avoid condition, or appears in the vicinity of the smoking-related picture on 75% of trials in the attend condition, or appears with equal frequency in the vicinity of neutral and smoking-related pictures in the control condition. The inter-trial interval is jittered between 750 ms and 1,250 ms in order to reduce the monotony of the task. The sequence of events will be controlled using EPrime version 2 software (Psychology Software Tools Inc., Pittsburgh, Pennsylvania, United States), and the total task time is approximately 50 minutes.

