#### functional Magnetic Resonance Imaging(fMRI) acquisition

An anatomical and an fMRI scan will be performed on the test day session (day seven). During the fMRI cue exposure procedure, smoking-related and control cues will be presented in a boxcar design with four blocks per category (Figure 2). Participants are required to make a button press on each stimulus presentation to identify they have seen the image (this does not terminate viewing time). Each block will be 40 seconds in length, during which time eight cues will be presented. Before and after each block, a crosshair will be presented for five seconds. Participants will then be asked to rate their craving level on an eight-point scale (‘none at all’ to ‘extreme’). The scale will be presented for 10 seconds followed by presentation of a crosshair for another 10 seconds. Thus, the total between-block interval is 25 seconds. The sequence of events will be controlled using EPrime version 2 software (Psychology Software Tools Inc., Pittsburgh, Pennsylvania, United States), and the total task time is approximately 10 minutes. The total MRI protocol will last approximately 15 minutes.

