Each participant’s fMRI data will then be entered into a first-level voxel-by-voxel analysis using the general linear model. Each cue block (smoke or control) will be modelled as a boxcar function convolved with a canonical hemodynamic response function that begins at the onset of the first cue in the block and ends at the end of the block (60-second duration). A high-pass filter will be applied to remove slow signal drift. A smoking-related cue greater than control cue contrast image will then be created and inputted into a random effects analysis. A two (varenicline and placebo) × three (attend, avoid, and control) mixed-model analysis of variance (ANOVA)will be used to examine smoking cue reactivity (smoking greater than control) between each group. Voxel-wise analysis will be conducted within an Region of Interest (ROI) mask. The mask will be created from anatomical regions identified in a meta-analysis of cue reactivity [31]: nucleus accumbens, caudate, putamen, temporal gyrus, anterior cingulate gyrus, amygdala, insula, posterior cingulate cortex, inferior frontal gyrus, and angular gyrus. Each bilateral region will be selected using the WFU PickAtlas tool [32] and combined to create the mask. Resulting activations will be considered significant at an alpha level of 0.001 (uncorrected) with a minimum cluster extent threshold of 20 contiguous voxels. *Post hoc* analyses of parameter estimates will be used to evaluate the nature of significant effects. Smoking cue greater than control cue contrast images for each participant will also be input into random effect regression analyses examining relations between post-training cognitive bias scores and neural cue reactivity.

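### The dot-probe co-primary is analysed as pre/post change; adjusting for the pre-CBM score and sex would estimate the CBM effect more precisely for one or two degrees of freedom

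*Protocol article*

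**What the plan says.** The Outcome measures section names two primary outcomes: "Primary outcome measures are changes in cognitive bias as measured by the visual dot-probe task, and neural responses to smoking-related cues".

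- **Dot-probe.** Cognitive bias analyses: "These bias scores will be used to examine cognitive training effects in a two (pre- and post-CBM) × two (varenicline and placebo") with the three CBM groups as the remaining factor. Both scores come from the training session: "Half of the test trials (n = 128) are presented prior to the training trials, and half (n = 128) after the training trials" (Cognitive bias modification). Data collection procedures puts the first measurement on the test day, after the drug week and before randomisation to CBM.
- **fMRI.** One scan only: "An anatomical and an fMRI scan will be performed on the test day session (day seven"). The second-level model is a drug × CBM "mixed-model analysis of variance (ANOVA)will be used to examine smoking cue reactivity (smoking greater than control) between each group".
- **Sex.** Randomization: "Randomization will be stratified so that equal numbers of male and female participants will be allocated to each experimental cell". Sex appears in none of the models listed for dot-probe, Stroop, questionnaires or fMRI. The Background reports that attenuated craving in the earlier CBM study was seen "in a subsequent cue exposure test (male participants only").

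**The concern.** When a mixed ANOVA has only two time points, its time × CBM interaction is the between-group test on post minus pre. That subtracts the whole pre-CBM score, including its measurement noise. ANCOVA subtracts only the part that predicts the post-CBM score. A valid baseline is collected, and the stated model does not make the best use of it. The factor used to stratify allocation is also left out of the stated models.

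What is at stake is the width of the interval for each CBM effect, and power for hypotheses 1 and 2. These are separate directional claims, one for attend training and one for avoid training, so the single linear trend used for the sample size does not cover them.

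**Working it through.** **Inputs from the Sample size determination section.** Expected change is +30 ms (attend), −30 ms (avoid) and 0 ms (control); n = 30 for more than 80% power at alpha 0.05. No SD is given. Planned size is 72, so 24 per CBM group. The pre-post correlation ρ is not in the document; 0.3, 0.5 and 0.7 are assumed below.

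**1. The plan's own figure.** The n = 30 claim cannot be reproduced without an SD, but it can be solved backwards. With equal groups the linear contrast is attend minus avoid, 30 − (−30) = 60 ms. Its standard error is SD × √(2/10), on 27 df. Two-sided power is 80.3% at SD 46 ms and 79.9% at 46.2 ms. So the claim implies an SD of change of at most about 46 ms. This is an upper bound, because the plan says more than 80%.

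**2. Relative variance.** Let s₁ and s₂ be the within-group SDs of the pre and post scores.
- Change: s₁² + s₂² − 2ρs₁s₂
- ANCOVA: s₂²(1 − ρ²)
- Difference: (s₁ − ρs₂)², which is never negative

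With s₁ = s₂ = s, the ratio ANCOVA/change is s²(1 − ρ²) / 2s²(1 − ρ) = (1 + ρ)/2.

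| ρ (assumed) | Variance ratio | With small-sample penalty (×(1 + 1/64)) | 72 on change equals, by ANCOVA |
|---|---|---|---|
| 0.3 | 0.65 | 0.66 | 47 |
| 0.5 | 0.75 | 0.76 | 54 |
| 0.7 | 0.85 | 0.86 | 61 |

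The last column is 72 × the unpenalised ratio. Simulation of the 2 × 3 design gave ratios of 0.67, 0.75 and 0.85, with both estimators unbiased for the CBM effect.

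**3. Power for one pairwise difference of 30 ms**, 24 per group, two-sided 0.05. The ANCOVA SD is SD of change × √((1+ρ)/2).

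| SD of change | Change score | ρ = 0.3 | ρ = 0.5 | ρ = 0.7 |
|---|---|---|---|---|
| 46 ms | 60% | 78% | 72% | 67% |
| 40 ms | 72% | 88% | 84% | 79% |

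At 46 ms, the difference between two groups detectable with 80% power falls from 37.9 ms to 30.8, 33.1 and 35.2 ms.

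**4. Power for the contrast used in the sample size.** At 46 ms and 24 per group, the 60 ms linear contrast has 99.4% power on change scores. The omnibus time × CBM test has 98.3%. Here ANCOVA can add less than two percentage points.

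**5. The drug effect.** The pre-CBM score follows seven days of drug. If drug shifts bias by −15 ms both before and after CBM (an illustrative value), the ANCOVA drug coefficient is about −15 × (1 − ρ): −10.5, −7.5 and −4.5 ms. Simulation gave −10.4, −7.6 and −4.5. In the change score the shift vanishes. The pre-CBM score is therefore a clean covariate for CBM but not for drug.

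**6. Cost.** A 2 × 3 design with 72 people has 66 error df; the pre-CBM score leaves 65, and sex leaves 64. Losing one of these raises the squared critical t by about 0.06%.

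**The case against.** The strongest reply is that the contrast the plan was sized for does not need help. Step 4 bears this out, and 46 ms is the largest SD the plan allows, so 60% is the low end for a pairwise comparison. That limits the size of the point. It does not remove it, because hypotheses 1 and 2 treat attend and avoid separately, and interval width matters whatever the power.

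It can also be said that covariates belong in an analysis plan that is not shown. This carries weight for sex. It carries less for the dot-probe model, because the article states that model outright and it is the stated choice that is less efficient.

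Several stronger readings are tempting, and the document does not support them:

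- *All primary analyses use change scores.* There is one scan, after CBM, so the neural outcome on which the primary objective rests has no change score.
- *Leaving out sex inflates the error in every model.* A stable sex difference in level cancels from time × CBM. Sex helps there only if it predicts change, and nothing in the document says that it does.
- *The male-only result shows that sex matters for these outcomes.* It concerned craving to in vivo cues. The reduction in bias is reported for daily smokers without a sex limit, and no hypothesis here involves sex.
- *The trial could not look at sex.* Allocation is balanced by sex in each cell, so an exploratory analysis remains possible.
- *Adjustment is free.* It costs one or two df and requires a separate drug analysis.

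**Conclusion.** The point holds as a loss of precision in the CBM effect on the dot-probe co-primary, and it is worth correcting. With equal pre and post variances, the planned test is less precise than ANCOVA at any correlation below 1: ANCOVA needs 15% to 35% less variance over ρ = 0.7 to 0.3. At the 46 ms bound, power for either pairwise 30 ms difference rises from about 60% to between 67% and 78%; the linear contrast barely moves. These figures rest on assumed values of ρ and on an SD inferred from the n = 30 claim.

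A reader might infer bias or an invalid test. Neither follows: the planned CBM tests are valid, and omitting a balanced stratification factor tends, if anything, to make them conservative. For fMRI the gain from adding sex depends on how far sex predicts neural response, which the document does not state.

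**What to change.** 1. **Dot-probe, CBM effect:** analyse the post-CBM bias score on CBM, drug, CBM × drug and sex, with the pre-CBM score as covariate.
2. **Modified Stroop interference, and QSU and VAS across CBM:** the same form of model, each with its own pre-CBM value as covariate.
3. **Drug effect on bias:** do not read it from the adjusted model; test drug on the day-seven pre-CBM score itself.
4. **fMRI:** add sex to the second-level 2 × 3 model.
5. **Optional:** report CBM × sex, labelled exploratory.

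The cost is a change of wording, one or two error degrees of freedom and one separate drug analysis. No new data are needed.

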#### Questionnaire analyses

To assess group differences at baseline two (varenicline and placebo) × three (attend, avoid, and control) between-subject ANOVAs will be conducted on EPQ-R, QSU, MNWS and VAS data. Mood (VAS) and craving (QSU and VAS) data will be analyzed in two time-phase analyses using ANOVA. We will first assess general (i.e., not cue-related)cravingacross drug treatment using baseline data from sessions one and two in a two (pre- and post-drug treatment) × two (varenicline and placebo) mixed-model ANOVA. We will also examine craving and mood change across CBM in a two (pre- and post-CBM) × two (varenicline and placebo) × three (attend, avoid, and control) mixed ANOVA, in which time is a within-subjects factor and drug is a between-subjects factor.

## Discussion

This study will investigate the neural effects of smoking-related CBM in daily smokers. We will also examine whether one-week’s treatment of the licensed smoking cessation pharmacotherapy varenicline alters neural response to smoking-related cues. Within this data set, we will be able to explore whether there is any pattern suggesting an interactive effect of CBM and varenicline. These are novel questions in this field and will inform future research with a better understanding of the mechanisms that may underlie CBM. As CBM is a treatment which can be delivered remotely via computers, tablets, or smartphones it could therefore provide a cost-effective intervention that could be used, in conjunction with more traditional pharmacotherapies and behavioral support, to help promote long-term smoking cessation and reduce relapse rates.

This study will recruit daily smokers who are not currently trying to quit smoking. Therefore this is an analogue sample and participants have not been recruited on the basis of seeking cessation support. The primary reason for this is due to the proposed mechanism by which varenicline impacts on cue reactivity. Although this mechanism has not been unequivocally established, it is suggested that smoking cues lose incentive salience during varenicline treatment due to its attenuation of smoking reinforcement. That is, individuals experience reduced reward from smoking and this is associated with drug-related cues. For this process to occur however, individuals need to smoke to experience the attenuated smoking reinforcement. For the purposes of this study, it was not considered ethical to enroll smokers motivated to quit as their participation may maintain smoking and delay a quit attempt. Recruitment of non-quitting smokers also avoids interference of other smoking-related treatments such as nicotine replacement therapy or behavioral support. This study will provide a basis to examine treatment effects of varenicline and CBM on cognitive bias and cue-related responses that can inform future research in quitting populations.

## Trial status

As of March 2014, 55 participants have been enrolled onto the study. The first participant was enrolled in November 2012 and completion of data collection is projected for June 2014.

## Abbreviations

ANOVA: Analysis of variance
CBM: Cognitive bias modification
EPQ-R: Eysenck personality questionnaire-revised
FWHM: full width at half maximum
fMRI: functional Magnetic Resonance Imaging
MNWS: Minnesota nicotine withdrawal scale
NRT: Nicotine replacement therapy
QSU: Questionnaire of smoking urges
RT: Reaction time
ROI: Region of interest
SPM: Statistical parametric mapping
VAS: Visual analogue scales.
